## Abstract

**Background:**

Tinnitus occurs in a large part of the general population with prevalences ranging from 10% to 15% in an adult population. One subtype is cervicogenic somatic tinnitus, arising from cervical spine dysfunctions, justifying cervical spine assessment and treatment. This study aims to investigate the effect of a standardized physical therapy treatment, directed to the cervical spine, on tinnitus. Additionally, a second aim is to identify a subgroup within the tinnitus population that benefits from physical therapy treatment.

**Methods and design:**

This study is designed as a randomized controlled trial with delayed treatment design. Patients with severe subjective tinnitus (Tinnitus Functional Index (TFI) between 25 and 90 points), in combination with neck complaints (Neck Bournemouth Questionnaire (NBQ) >14 points) will be recruited from the University Hospital of Antwerp.

Patients suffering from tinnitus with clear otological etiologies, severe depression, traumatic cervical spine injury, tumors, cervical spine surgery, or conditions in which physical therapy is contra-indicated, will be excluded.

After screening for eligibility, baseline data such as TFI, NBQ, and a set of cervical biomechanical and sensorimotor tests will be collected.

Patients are randomized in an immediate therapy group and in a group with a delayed start of therapy by 6 weeks.

Patients will receive physical therapy with a maximum of 12 sessions of 30 min for a 6-week program. Data from the TFI and NBQ will be collected at baseline (week 0), at the start of therapy (weeks 0 or 6), at the end of therapy (weeks 6 or 12), 6 weeks after therapy (weeks 12 or 18), and 3 months after therapy (weeks 18 or 24). Secondary outcome measures will be collected at baseline and 6 weeks after the therapy (weeks 12 or 18), as the maximal therapy effect on the cervical spine dysfunctions is expected at that moment.

**Discussion:**

This study is the first to investigate the effect of a standardized physical therapy treatment protocol on somatic tinnitus with a prospective comparative delayed design and with blinded evaluator for baseline, end of therapy, and 6 and 12 weeks after therapy.

**Trial registration:**

12 September 2013, ClinicalTrials.gov: NCT02016313

## Background

Tinnitus is the phantom sensation of sound, in the absence of overt acoustic stimulation [1]. It occurs in 10% to 15% of the adult population [2].

Tinnitus can be related to many different etiologies such as hearing loss, a noise trauma, or the tinnitus may be related to the somatic system of the cervical spine or the temporomandibular area [2].

This study will focus on physical therapy treatment for patients suffering from chronic non-fluctuating subjective cervicogenic somatic tinnitus (CST).

The existence of a link between the cervical spine and tinnitus can be assumed based on several prior studies. Connections between the dorsal column of the spinal cord and the cochlear nuclei (CN) have been found in several animal studies [3,4]. These axons of the dorsal column originate from the C1-C8 dorsal roots of the spinal cord. In particular, stimulation of the C2 dorsal root ganglion generates responses from cells in the CN [5]. Additionally, Matsushima et al. [6] demonstrated that tinnitus improved in 52% of the patients after an occipital nerve block. Other recent studies in humans found that in some patients tinnitus could be evoked or modulated by input from the somatic system, for instance by forceful muscle contractions of the head, neck, and limbs, and pressure on myofacial triggerpoints [7-10]. These findings might explain the ability of some tinnitus patients to modulate their tinnitus by certain head or neck movements. For example, some patients indicate that their tinnitus worsens when performing a combined cervical spine extension and rotation.

Several research groups have investigated the effect of cervical spine treatments on CST [11,12]. Regarding physical therapy treatments, few scientific data are available. Sanchez et al. [11] reviewed five case reports in which cervical spine mobilizations and stretching of suboccipital muscles could decrease the intensity of the tinnitus in five patients. Latifpour et al. [12] showed in a randomized controlled trial (RCT) of 13 tinnitus patients and 11 controls, a greater improvement in tinnitus loudness after application of stretching, posture exercises, and acupuncture compared to controls (*P* >0.001).

Although only case reports and one RCT are reported, the ability of physical therapy treatment directed to the cervical spine to reduce the tinnitus seems promising.

Consequently, the aim of this study is to investigate the effect of a standardized physical therapy treatment program directed to the cervical spine, on several tinnitus and neck related parameters. Additionally, a second aim is to identify a subgroup within the tinnitus population that benefits from the physical therapy treatment.

## Methods

### Patients

Patients will be recruited from the University Hospital of Antwerp by otolaryngologists at their tertiary tinnitus clinic. During this consult, patients will be thoroughly tested to exclude any objective causes of the tinnitus. Patients will be included when suffering from severe chronic non-fluctuating subjective CST, which has been stable for at least 3 months, combined with neck complaints. The severity of the tinnitus will be evaluated using the Tinnitus Functional Index (TFI) [13]. Severe tinnitus is defined as a score between 25 and 90 on the TFI [13]. The presence of a significant neck complaint will be objectified using the 14 points cutoff point of the Neck Bournemouth Questionnaire (NBQ) [14,15]. Patients will be excluded when suffering from objective tinnitus, subjective tinnitus with etiologies, such as hearing loss or Meniere’s disease, severe depression (diagnosed by a psychologist), progressive middle ear pathology, intracranial pathology, traumatic cervical spine injury, tumors, cervical spine surgery, or any cervical spine condition in which physical therapy treatment is contra-indicated. Given the treatment that is studied, patients will also be excluded if they received physical therapy treatment directed to the cervical spine in the past 2 months.

### Study design

This study is designed as an RCT to evaluate the effectiveness of a standardized cervical spine treatment on tinnitus and neck-related parameters in patients suffering from CST. A delayed treatment design (Figure 1) will be used to create a waiting list to obtain the data for the control group [16]. At baseline, patients are randomly assigned by the responsible researcher to receive immediate treatment or to the waiting list. In part 1, the immediate treatment group receives the cervical spine treatment for 6 weeks. In part 2, the patients on the waiting list receive cervical spine treatment for the next 6 weeks. The immediate treatment group now enters a 6-week follow-up period. In part 3, all patients enter a follow-up period which ends 12 weeks after the last treatment session.

**Figure 1 F1:**
[figure not shown]
**Delayed treatment design.** Q: Questionnaires. Exam: cervical spine examination.

A pilot study was used for calculating the sample size needed and to optimize the inclusion as well as the follow-up measuring procedure.

The results of the trial will be reported according to the CONSORT guidelines.

### Randomization procedure

After the baseline measurements, the patients are randomized into the immediate treatment group or into the waiting list in a 1:1 ratio based on a block randomization with variable block lengths. The responsible researcher generated a randomization list with Microsoft Excel® software (version 14.3.5, 2010 © Microsoft Corporation). The randomization list is only accessible for the responsible researcher.

### Ethical approval and consent

Ethical approval was obtained from the ethics committee of the University Hospital of Antwerp (reference number: B300201421113). The names of all ethical bodies that approved the study can be found in the additional file. Informed consent is obtained for all patients. The trial is currently in the recruitment phase.

### Outcome measures

The primary outcome measures are the TFI [13] and NBQ [14].

The TFI focuses on eight different domains: the unpleasantness of the tinnitus; reduced sense of control; cognitive interference; sleep disturbance; auditory difficulties attributed to the tinnitus; interference with relaxation; reduction in quality of life; and emotional distress. The test-retest reliability of the TFI is good (r: 0.78). The convergent validity with the Tinnitus Handicap Inventory (r: 0.86) and Visual Analogue Scale (r: 0.75) is good, as well as the discriminant validity with the Beck Depression Inventory-Primary Care (r: 0.56). The clinically relevant reduction was a 13-point reduction.

The pilot study showed that the studied treatment had most influence on the ‘reduced sense of control’ and ‘interference with relaxation’ subscales. Consequently, special attention to these subscales will be paid.

The secondary outcome measures will be the NBQ, a set of different biomechanical and sensorimotor neck parameters and the tinnitus loudness.

The NBQ [14] consists of seven questions on the severity of the neck complaint and its interference with the patient’s wellbeing and professional and daily activities. The test-retest reliability of the NBQ is moderate (ICC: 0.65). The construct validity was acceptable with both the Neck Disability Index (r: 0.50) and the Copenhagen Neck Functional Index (r: 0.44). The effect size was found to be high (Cohen’s d: 1.67), which indicates that the NBQ is highly responsive to changes in cervical spine complaints.

For measuring the biomechanical and sensorimotor neck parameters, the cervical spine mobility will first be investigated in the three cardinal planes.

The range of motion (ROM) is registered using a VICON® measuring device. This device uses the reflection of ultraviolet light on applied markers to perform a 3D movement analysis. The mean absolute error of this measuring device in dynamic conditions is 0.48° (SD 0.05°).

Second, the sensorimotor control of the cervical spine will be measured using the head repositioning accuracy (HRA) to the neutral head position and the continuous linear movement test (CLMT). The HRA measurement will be executed as described by Revel et al. [17] in 1991. The VICON® will be used to register the joint position errors.

The continuous linear movement test (CLMT), as described by Sjolander et al. [18], will be used to objectify the movement speed, acceleration, and Jerk index using the VICON® data. Special attention will be paid to the movement speed and acceleration, as these parameters have proven to have good test-retest reliability [19].

Third, a set of tests will be executed to objectify the impairments in cervical spine mobility and muscle function. This set of tests includes a manual investigation of the cervical spine, tenderness of trigger points, and a strength and endurance test of the deep neck flexor muscles [20]. The manual investigation consists of a manual rotation test and adapted Spurling test [15], and a flexion rotation test evaluating the upper cervical spine rotation mobility [21]. The tenderness of 16 trigger points, is investigated by applying manual pressure [22]. The strength and endurance of the deep neck flexor muscles is objectified using the craniocervical flexion test [20].

All outcome measures will be documented at baseline and at 12 weeks. The primary outcome measures will additionally be documented at 6 and 18 weeks.

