#### Sample size and power

The sample size was calculated using Medcalc (Medcalc Software bvba.). This calculation was based on data of the primary outcome measure, obtained in a pilot study of 14 patients. Sample size calculation was performed for the clinically relevant change of 13 points in TFI score. The sample size was calculated for the study to have 80% power to reject the null hypothesis (H_0_). The type I error probability, associated with this test, is 0.05. To achieve the 80% power, 17 patients are needed in each group.

The primary analysis population is the intention-to-treat population. This population includes all randomized patients who provided baseline data, regardless of whether or not they adhere to the complete protocol.

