#### Statistics

The primary statistical hypotheses are:

H_0_: Change in TFI-baseline to TFI-6 weeks (treated) = Change in TFI-baseline to TFI-6 weeks (waiting list)

Change in NBQ-baseline to NBQ-6 weeks (treated) = Change in NBQ-baseline to NBQ-6 weeks (waiting list)

The primary outcome is a change in the scores on the TFI and NBQ after 6 weeks. The mean change in TFI and NBQ-baseline and TFI and NBQ 6-week follow-up scores will be calculated.

This mean change in TFI and NBQ scores of the treated group will be compared to the mean change in TFI and NBQ scores of the waiting list group.

A repeated measures ANOVA and post hoc tests will be used to compare the mean changes of the treatment and waiting list population at 6 weeks and secondary at baseline, 12, and 18 weeks follow-up.

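### NBQ is both a primary and a secondary outcome while the sample size rests on TFI alone, so either the familywise error or the power departs from its stated figure, depending on a success rule the article does not give

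*Protocol article*

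**What the plan says.** The Outcome measures section opens with "The primary outcome measures are the TFI [13] and NBQ [14". After describing the TFI, the same section states "The secondary outcome measures will be the NBQ, a set of different biomechanical and sensorimotor neck parameters and the tinnitus loudness".

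The Statistics section treats NBQ as primary. Under the primary hypotheses it lists a TFI null hypothesis and a second one, "Change in NBQ-baseline to NBQ-6 weeks (treated) = Change in NBQ-baseline to NBQ-6 weeks (waiting list". It then says "The primary outcome is a change in the scores on the TFI and NBQ after 6 weeks".

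The Sample size and power section treats TFI as the only primary outcome:
- On the source of the data: "This calculation was based on data of the primary outcome measure, obtained in a pilot study of 14 patients", with the outcome in the singular.
- On the effect: "Sample size calculation was performed for the clinically relevant change of 13 points in TFI score", with no counterpart for NBQ.
- On power: "The sample size was calculated for the study to have 80% power to reject the null hypothesis", meaning one hypothesis.
- On alpha: "The type I error probability, associated with this test, is 0.05", again for one test.

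The result is 17 patients per group. No NBQ difference, SD or power is given. The Discussion gives a total of 40 patients.

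Two statements on timing bear on the point. The end of Outcome measures reserves the week-6 and week-18 measurements for the primary outcomes. The abstract (Methods and design) schedules TFI and NBQ together at every visit.

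**The concern.** The status of NBQ decides what counts as a positive trial, and the article gives two incompatible answers. Reading further does not settle it: Statistics points to two primary outcomes, and Sample size and power points to one.

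The choice could matter in practice. The treatment is directed at the neck, the article describes NBQ as highly responsive to change in neck complaints, and the Discussion reports that pilot changes in total TFI were small. A trial positive on NBQ and null on TFI is therefore plausible. As written, that result could be called a success, a failure or a secondary finding, and the choice could be made after the data are seen. The stated 5% and 80% describe the TFI test. Whether they describe the primary objective depends on a rule that is not stated.

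**Working it through.** **Inputs from the article.** Difference 13 TFI points; power 80%; alpha 0.05; 17 per group (Sample size and power). Total 40, that is 20 per group at 1:1 (Discussion; Randomization procedure).

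**Assumptions.** Two-sided test, because sidedness is not stated. Neither SD is stated. The NBQ effect and the correlation between the two test statistics are shown as ranges.

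**1. The plan's own figure.** Without an SD, 17 per group cannot be reproduced forward, so I solved backward.
- Normal formula: n = 2(1.960 + 0.842)² / d². With n = 17, d = 2.802 × √(2/17) = 0.961, and SD = 13 / 0.961 = 13.5.
- Noncentral t, 17 per group: d = 0.991, and SD = 13 / 0.991 = 13.1.

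So 17 per group fits one two-sided TFI test with an SD of about 13. The steps below use the t-test value.

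**2. Success if either outcome is significant, each at 0.05.** Familywise error when both nulls are true = 1 − P(|Z₁| ≤ 1.96 and |Z₂| ≤ 1.96). If independent, this is 1 − 0.95² = 9.75%.

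| Correlation | 0 | 0.3 | 0.5 | 0.7 | 0.8 |
|---|---|---|---|---|---|
| Familywise error | 9.75% | 9.5% | 9.1% | 8.3% | 7.8% |

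The chance of at least one significant result cannot be lower than the TFI power of 80%, so power does not fall.

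**3. Success only if both are significant, each at 0.05.** The chance of a false claim stays within 5%. Joint power cannot exceed the TFI power, 80% with 17 per group. If NBQ also had 80% power, joint power = P(Z₁ ≤ 0.842 and Z₂ ≤ 0.842). If independent, this is 0.80 × 0.80 = 64%.

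| Correlation | 0 | 0.3 | 0.5 | 0.7 | 0.8 |
|---|---|---|---|---|---|
| Joint power | 64% | 67% | 69% | 71% | 73% |

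The article does not support 80% power for NBQ. Over assumed standardised between-group NBQ effects, 17 per group and independence:

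| NBQ effect d | 0.5 | 0.8 | 1.0 |
|---|---|---|---|
| NBQ power | 29% | 62% | 81% |
| Joint power (0.80 × NBQ power) | 23% | 49% | 65% |

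With 20 per group analysed, TFI power is 86.3%. If NBQ had the same power and were independent, joint power would be 0.863 × 0.863 = 74.5%. For 80% joint power with equal effects and independence, about 22 per group (44) are needed.

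**4. Alpha split equally, 0.025 per outcome.** Familywise error is held at 5%. TFI power for 13 points is:
- 17 per group: 70.3%.
- 20 per group: 78.5%.
- 80% needs 21 per group (42 in total).

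**5. TFI as sole primary outcome.** One test at 0.05 with 17 per group: the stated 5% and 80% stand.

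**The case against.** **A reader might infer that the stated type I error and the stated power both fail.** The document does not support that. Steps 2 to 4 show that each success rule breaks one property and leaves the other: an either-outcome rule raises error without lowering power, while a both-outcomes rule or a split alpha lowers power without raising error. It is also an inference that the two hypotheses share one alpha of 0.05. The article ties that figure to the TFI calculation and states no alpha for NBQ.

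**Multiplicity handling is commonly left to an analysis plan, and none is shown.** This stands: a missing alpha allocation alone would be no finding. What remains is a contradiction between statements the article does make, namely NBQ as primary and as secondary, and two primary hypotheses against a calculation for one.

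**A reader might also say that a neck-only benefit would be out of place in a tinnitus trial.** That goes too far. The Background, Study design and Discussion sections state the aim as an effect on tinnitus and neck-related parameters, so NBQ lies within the objective. The difficulty is only that its rank is undecided.

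**The power loss may be small.** This partly stands. If all 40 patients are analysed, halving alpha leaves TFI power within 2 points of 80%. The article does not say whether the six patients beyond 34 are a dropout allowance, so 70% to 78.5% is the fair range.

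**NBQ might be amply powered, given the d of 1.67 in Outcome measures.** That figure describes the questionnaire's responsiveness to change. It is not a between-group effect and cannot be used as one.

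**Conclusion.** The point holds, and should be fixed, in this form: the status of NBQ is contradictory, two primary hypotheses are stated, and the sample size covers TFI only. Depending on the unstated success rule, one stated property fails for the primary objective:
- Either outcome suffices: familywise error up to 9.75%, or 8.3% at correlation 0.7.
- Both required: joint power at most 80% with 17 per group. It is 64% to 71% at correlation 0 to 0.7 if NBQ also has 80% power, and lower if it does not.
- Alpha halved: TFI power about 70% with 17 per group, or 78.5% with 20.

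These figures assume a two-sided test, and the TFI power figures also use the back-solved SD of about 13.1. The correlation and the NBQ effect are unknown and are given as ranges. Confidence is high for the contradiction, which needs no assumption. The size depends on the rule the sponsor intended.

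**What to change.** Make the week-6 comparison of TFI change the single primary hypothesis at two-sided 0.05, as the sample size already assumes. Make NBQ the first secondary outcome, tested at 0.05 only if TFI is significant. This fixed order holds the error across the two outcomes at 5% and needs no more patients.

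The edits must go together:
- Outcome measures, opening sentence: remove NBQ.
- Statistics: remove NBQ from the primary null hypotheses and from the sentence defining the primary outcome, and state the testing order.
- Outcome measures, closing sentences: reword so that NBQ is still measured at 6 and 18 weeks, consistent with the abstract's joint schedule for TFI and NBQ. As written, those visits belong to primary outcomes only, so demoting NBQ without this change would drop its week-6 value from that section's schedule.

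The cost is wording in the protocol and analysis plan, and a registry update if needed. NBQ loses co-primary status. The article says recruitment is under way, so the change should be made before outcome data are examined.

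If the sponsor prefers to keep NBQ co-primary, that is also valid. It should then remove NBQ from the secondary list, state the success rule and alpha allocation, and restate the power for that rule with an NBQ difference and SD.

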### Intervention

The intervention, a physical therapy treatment directed to the cervical spine, consists of a multimodal care containing manual mobilizations, exercise therapy, and home exercises. This multimodal physical therapy treatment is based on recent insights of cervical spine therapy [23-25]. Additionally, patients are instructed to perform exercises at home. For these exercises, a booklet established by Castien et al. [26] was adjusted for the tinnitus patients, implementing exercises for the deep neck flexor muscles (Figures 2 and 3) [27] and self-mobilizing exercises [28].

**Figure 2 F2:**
[figure not shown]
**(a) Craniocervical flexion exercise in supine position (starting position). (b)** Craniocervical flexion exercise in supine position (end position).

**Figure 3 F3:**
[figure not shown]
Craniocervical flexion exercise in sitting position.

Treatment will be applied by a selected group of physical therapists that all obtained a master’s degree in physical therapy and an additional master’s degree in manual therapy. Moreover, they all participated in a training session organized by the research group. During this training session, the treatment protocol was discussed and trained. Patients included in the trial will be referred for treatment to one of the selected therapists (guided referral). The treatment protocol provides a maximum of 12 standardized physical therapy treatment sessions. The therapists are free to adapt the mobilization techniques and exercises to the current situation of the patient. The therapist registers all performed techniques and exercises.

